8	Using What Has Been Learned to Deal with Future Moods: Participants discuss how they will keep the momentum of their practice going. Therapists distribute information about settings where group mindfulness practice can be continued.	Support for Continuing Practice: Participants review the course and plan for maintaining gains including all components of HEP. Participants review their goals with the dietician.+

*USDA = United States Department of Agriculture.

+ The original HEP protocol was amended to include Nutrition in session 8.

TAU augmentation for both treatment groups was identical and consisted of medication management and supportive counseling delivered by third or fourth year psychiatric residents, attending psychiatrists or primary care physicians. Supportive therapeutic approaches aid in patients addressing problems without direct input from providers. Providers offer patients encouragement and guidance but do not engage in any therapeutic strategy other than active listening and offering support by focus on patients’ problems and concerns. Routine TAU visits are less than 30 minutes in duration and at intervals of one to three months. Participants were allowed to make medication changes during the acute and follow-up periods, with reporting of such changes on a regular basis. These changes will be incorporated into the analyses.

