#### Mediators, moderators and potential covariates

A number of other psychometric variables believed to be associated with mindfulness were investigated and measured at baseline, during mid-point (week 4), after the end of treatment (week 8) and the long-term follow-up weeks 24, 36, and 52. The following potential mediators related to MBCT were measured: mindfulness with the Five Facet Mindfulness Questionnaire [42]; experiential avoidance with the Acceptance and Action Questionnaire (AAQ) [43]; rumination with the Ruminative Response Scale (RRS) [44,45]; and self-compassion with the Self-Compassion Scale (SCS) [46].

Psychiatric factors that may impact depression severity and resistance such as early age of depression onset, number of recurrences, poor treatment outcomes (e.g. incomplete remission) and co-morbid psychiatric illness (e.g. anxiety disorders [47] or personality disorders [48]), will be included in the analysis as covariates [49]. Also included will be other factors known to be moderators of depression treatment outcomes. These include demographic factors such as minority status, ethnicity and lower socio-economic status [50] and stress, both current [51,52] and a childhood history of stress [53] (trauma, abuse, neglect) which were collected during the baseline assessment.

Medication changes in the TAU arm are the same ones utilized in treating persisting or worsening depression in the STAR*D studies [3,8]. Changes were tracked during the 8-week treatment and over the 52 week follow-up through patient report and chart review. Alternate forms of treatment (i.e. individual psychotherapy, group psychotherapy, electroconvulsive therapy, etc.) for depression was tracked after the treatment-phase of the study through patient report and interview. These treatments will be analyzed as covariates as well as secondary outcomes, similar to the aforementioned medication changes.

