Additional secondary analyses will test for effects of time. These models will also include indicator variables of any additional treatments (e.g. HEP participants’ crossing over to take MBCT outside of the research), medication changes after the end of acute treatment before the 24, 36 and 52-week follow-ups and also whether or not patients began new psychotherapeutic interventions after treatment or continued formal meditation practices.

Based on the extent and nature of missing data (outcomes, predictors, baseline, and items from scales), we will use one of several strategies for data analysis. We anticipate that the majority of missing data will result from participant attrition. In this case, we will know the randomization assignment and have data from some, but not all, of the planned assessments. Our primary approach to dealing with this monotone missing data pattern will be a pattern-mixture modeling approach [60]. We may also be missing some data on predictors, even in the absence of participant attrition. Our primary method for dealing with missing predictor values will be multiple imputation using a regression modeling approach [60]. This method is superior to simpler methods such as using group means for missing data. In order to limit attrition, we will provide an incentive in the form of an assessment payment schedule to increase motivation to complete all assessments.

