### Limitations

The TAU intervention has some variance because we allowed medication changes to take place, which increases the possibility of wash-out effects of MBCT or falsely amplifying its effects. Moreover, antidepressants alone are also well documented to be associated with placebo effects, although these appear to be reduced in a TRD population [62]. Because our aim was to show that MBCT is an effective augmentation strategy and because we wanted trial results to be widely generalizable in light of routine clinical practice, we permitted some flexibility in medication changes. We anticipate that randomization and statistical analysis will control for this variance and allow us to compare the impact of medication changes in both arms.

The current investigation lacks a 3^rd^ arm or wait-list control condition, which limits the ability to determine whether factors unrelated to treatment, such as time or life events effects were associated with treatment effects. We will however, be able to compare our outcomes to similar TRD populations presented by Kenny and Williams [12] and Eisendrath et al., [13]. While we expect the association to be modest, we predict that treatment expectancies or patients’ initial beliefs about the success of either intervention could influence treatment outcomes. The current investigation lacks a measure of treatment preference, which could have played a predictive role in affecting clinical outcomes.

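### The additional 1-year models adjust for treatments and meditation practice that arise after randomisation, and nothing says the comparison by assigned arm is the governing 1-year estimate

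*Protocol article*

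**What the plan says.** The article treats follow-up efficacy in two places within Planned analytic approach.

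- It first plans to assess persistence at weeks 24, 36 and 52 with models that parallel the week-8 ones. The template spelled out there, for functional status, contains randomised condition, therapy group and baseline score. The moderators to be added are pre-treatment characteristics. No variable arising after randomisation is listed.
- It then adds: "Additional secondary analyses will test for effects of time". The next sentence reads "These models will also include indicator variables of any additional treatments", with HEP participants taking MBCT elsewhere as the example. The list continues with "medication changes after the end of acute treatment before the 24, 36 and 52-week follow-ups" and with "whether or not patients began new psychotherapeutic interventions after treatment or continued formal meditation practices".

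Three other sections bear on the point.

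- Mediators, moderators and potential covariates says of non-study treatments: "These treatments will be analyzed as covariates as well as secondary outcomes, similar to the aforementioned medication changes". It states that medication changes were tracked during the 8 treatment weeks as well as through follow-up.
- Description of interventions says of medication changes in the acute and follow-up periods: "These changes will be incorporated into the analyses". It gives no method.
- Limitations says of the variability from medication changes: "We anticipate that randomization and statistical analysis will control for this variance".

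**The concern.** A covariate is safe to adjust for in a randomised comparison when it is fixed before allocation. The variables listed here are not, and the article itself supplies the links that make them a problem.

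- **Allocation to continued meditation.** Mindfulness training is in MBCT only (Table 1), and MBCT session 8 points participants to places where they can keep practising (Table 2). Adjusting for continued practice removes part of what MBCT is meant to deliver.
- **Allocation to crossover.** The article's own example can occur only in the HEP arm.
- **Response to medication change.** "Medication changes in the TAU arm are the same ones utilized in treating persisting or worsening depression in the STAR*D studies". Such changes follow from how the patient is doing, which allocation may already have altered.

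Conditioning on such variables does two things. It blocks the part of the effect that runs through them. It also compares unlike patients: those who continue meditating, or who change medication, may differ between arms in unmeasured prognosis. Whether gains last to one year is a stated aim (Research objectives) and a secondary outcome (Primary and secondary outcome measures). Two analyses with different meanings could give different answers to that question, and the article has no rule for choosing between them.

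**Working it through.** The plan gives no figure on this point to reproduce, and no rates of continued practice, crossover or medication change. The size can only be shown over assumed values.

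**Set-up** (400,000 simulated patients per scenario; outcome in SD units; negative favours MBCT; Monte Carlo standard error of the randomised contrast about 2/√400,000 = 0.003):

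- T = 1 for MBCT and 0 for HEP; u = unmeasured prognosis.
- Week-8 state S = d·T + 0.7u + noise.
- Continued meditation M: about 60% in MBCT and 10% in HEP, with log-odds shifted by -g·S.
- Rescue treatment R (medication change or new therapy): log-odds -0.5 + S.
- Follow-up score Y = d·T + b·M + r·R + 0.7u + noise, with r = -0.3.

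The randomised contrast is the coefficient of T in Y ~ T. The adjusted contrast is the coefficient of T in Y ~ T + M + R.

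**Check by algebra.** The randomised contrast should equal d + b(M1 - M0) + r(R1 - R0), where 1 and 0 denote the arm proportions.

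- Benefit wholly through practice: 0 - 0.8(0.598 - 0.099) - 0.3(0.398 - 0.398) = -0.399; simulated -0.402.
- Part direct, part through practice: -0.2 - 0.6(0.599 - 0.101) - 0.3(0.359 - 0.398) = -0.487; simulated -0.486.
- Benefit wholly direct: -0.5 - 0.3(0.304 - 0.399) = -0.472; simulated -0.471.

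**Results.**

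| Assumption | d | b | g | Randomised | Adjusted |
|---|---|---|---|---|---|
| Wholly direct; only rescue depends on severity | -0.5 | 0 | 0 | -0.47 | -0.46 |
| Wholly direct; milder patients continue more | -0.5 | 0 | 0.5 | -0.47 | -0.35 |
| Part direct, part through practice | -0.2 | -0.6 | 0 | -0.49 | -0.18 |
| Same; milder patients continue more | -0.2 | -0.6 | 0.5 | -0.49 | -0.09 |
| Wholly through practice | 0 | -0.8 | 0 | -0.40 | 0.00 |
| Same; milder patients continue more | 0 | -0.8 | 0.5 | -0.39 | +0.09 |

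**Stronger selection.** A second model has no direct effect and no rescue term, and lets u drive continuation directly (log-odds 0.4 in MBCT, -2.2 in HEP, minus g·u). With b from -0.6 to -1.0:

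- g = 0.5: randomised -0.29 to -0.48; adjusted +0.16.
- g = 1.0: randomised -0.26 to -0.45; adjusted +0.27.

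The most extreme setting tried (first model, stronger prognosis, g = 1.5) moved -0.34 to +0.30.

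**No true effect.** In the second model, changing b alters only the coefficient of M. The adjusted arm coefficient stays the same (0.163, 0.161 and 0.160 at g = 0.5 for the three values of b). Setting b = 0 therefore gives a randomised effect of 0 and the same adjusted values, +0.16 to +0.27, an apparent harm from MBCT. A separate simulation of 2 million patients, with continuation 59% against 11% and commoner in milder illness, gave +0.20.

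**Which covariate matters.** Adjusting for rescue treatment alone moved -0.471 to -0.461, which is 0.010/0.471 = 2%. With rescue assumed to have no effect on outcome, it moved -0.505 to -0.465, which is 0.040/0.505 = 8%. The separate simulation gave about 12%. Continued meditation does most of the damage.

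**The case against.** The strongest reply is about scope. The sentence on indicator variables follows directly on one about additional secondary analyses. The follow-up comparisons of the arms are planned just before it, and no such covariates are listed for them. A 1-year comparison by assigned arm is thus already in the plan. The medication indicator in that sentence is limited to changes after acute treatment, so it does not touch the week-8 primary test. The article also already intends to treat these treatments as secondary outcomes, and the full sentence in Limitations goes on to promise a comparison of medication changes between arms. A condensed article may leave the assignment of covariates to models to a fuller plan.

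Most of this stands. A reader might infer that all the 1-year efficacy models are adjusted in this way, or that medication changes during the 8 weeks are handled likewise. The article does not say either. It leaves both open, because the sections on covariates, on the interventions and on limitations speak of adjustment or incorporation without naming a model.

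A reader might also infer that the adjustment will reverse the sign of a true benefit. That needs benefit mainly through continued practice and continuation that depends on prognosis, and the article supplies neither. With rescue treatment alone the estimate hardly moves.

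The reply does not remove the core. The article states outright that these variables enter models, does not call those models exploratory, and does not say which 1-year estimate counts.

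**Conclusion.** The point holds for the additional secondary models over follow-up: their arm coefficient is not the randomised effect. On the assumed rates it could be nearly unchanged (-0.47 to -0.46), attenuated (-0.49 to -0.18), null (-0.40 to 0.00) or reversed (-0.39 to +0.09, and further under stronger selection into continued meditation). These figures show a range and do not predict this trial's result, since every behavioural rate and effect in them is assumed.

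The planned by-arm comparisons at weeks 24, 36 and 52, and the week-8 primary comparison, are not shown to be affected. What is missing for them is a statement that they govern and that the adjustment does not reach them. The expectation in Limitations is too hopeful on one count: randomisation balances what exists before allocation, and does not balance medication changes made afterwards in response to the patient's course.

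**What to change.** 1. State that the efficacy estimates at week 8 and at weeks 24, 36 and 52 are the comparisons by assigned arm already planned, with baseline covariates only, whatever later treatment participants received.
2. Remove the indicators for additional or crossover treatment, medication change, new psychotherapy and continued meditation from any model used to estimate the treatment effect. Report these variables by arm as outcomes, which the article already partly intends.
3. If a model that accounts for them is kept, label it exploratory or a sensitivity analysis and define what it estimates, for example the effect had no treatment been added, using inverse-probability weighting.
4. Align the statements in Description of interventions, in Mediators, moderators and potential covariates, and in Limitations with this.

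The cost is wording only; no new data are needed. The downside is that the main estimate then includes the effect of subsequent care. That fits the article's stated wish for results that carry over to routine practice, but it should be said when the result is reported.

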## Discussion

Treatment-resistant depression is a condition associated with high rates of disability, chronicity, reoccurrence and failed response to antidepressant treatment [3,8]. Through decreased workforce productivity and disability, the economic burden caused by refractory depression is enormous [10,61]; hence the importance of finding effective treatment modalities for this population is clear and of vital public health interest. This investigation represents the first RCT to evaluate MBCT for TRD. Results from this study will address whether MBCT is superior in reducing depression severity after 8 week treatment and improving relapse and remission rates over time in comparison to a credible comparator condition, developed to control for non-specific treatment effects. If successful, this study will identify an augmentation treatment for a large, hard-to-treat population for whom few treatments have been effective.

After analysis, we will be able to assess whether the specific constructs of a mindfulness-based intervention, such as the putative mediators in MBCT (increased mindfulness, self-compassion and decreased rumination and experiential avoidance) are enhanced more after an 8-week treatment with MBCT compared with HEP, and whether they are associated with positive treatment outcomes. We will also be able to evaluate whether treatment gains between groups (i.e. reduced depression severity, increased functional status) are retained during a 1-year follow-up and whether differential effects might be mediated by the specific constructs of MBCT listed above. Finally, we will be able to assess whether participant expectancy, treatment adherence (i.e. number of sessions attended), and compliance (i.e. number of minutes of homework completed) predicted treatment outcomes.

### Limitations

The TAU intervention has some variance because we allowed medication changes to take place, which increases the possibility of wash-out effects of MBCT or falsely amplifying its effects. Moreover, antidepressants alone are also well documented to be associated with placebo effects, although these appear to be reduced in a TRD population [62]. Because our aim was to show that MBCT is an effective augmentation strategy and because we wanted trial results to be widely generalizable in light of routine clinical practice, we permitted some flexibility in medication changes. We anticipate that randomization and statistical analysis will control for this variance and allow us to compare the impact of medication changes in both arms.

The current investigation lacks a 3^rd^ arm or wait-list control condition, which limits the ability to determine whether factors unrelated to treatment, such as time or life events effects were associated with treatment effects. We will however, be able to compare our outcomes to similar TRD populations presented by Kenny and Williams [12] and Eisendrath et al., [13]. While we expect the association to be modest, we predict that treatment expectancies or patients’ initial beliefs about the success of either intervention could influence treatment outcomes. The current investigation lacks a measure of treatment preference, which could have played a predictive role in affecting clinical outcomes.

### Summary

In summary, the results of this trial will address whether MBCT, previously shown to be effective for relapse prevention, may be an effective augmentation therapy for patients with TRD in active depressive episodes. In addition, this is the first RCT to compare whether MBCT is more effective in reducing depression, rates of relapse and disability when augmented by medications (TAU) than an active comparator condition; thereby isolating the elements of MBCT that might be most salient. In particular, the study will highlight whether mindfulness or other features of the interventions play important roles in the outcomes. In addition, the study will shed light on which MBCT factors play mediating roles in producing its effects. National self-report surveys have found complementary and alternative techniques such as mindfulness, are being used by 41% to 54% [63] of individuals with depression, indicating that there is substantial public demand for mindfulness-based treatment interventions. Consequently we believe the results of this study will have significant applications for depression care by informing providers about targeted, population-based non-pharmacological interventions strategies that may also be appealing to TRD patients.

## Abbreviations

TRD: Treatment-resistant depression; MBCT: Mindfulness-based cognitive therapy; HEP: Health-Enhancement Program; TAU: Treatment as usual; CBT: Cognitive behavioral therapy; RA: Research assistant; MBSR: Mindfulness-Based Stress Reduction; IRB: Institutional review board; PI: Principal investigator; DSMB: Data safety monitoring board; GEE: Generalized estimating equation.
